Improvement in self-awareness/mindfulness is proposed as a potential mechanism of action through which a yoga-based intervention improves mental health outcomes/depression
^
13
^. The training during yoga sessions will focus on improving self-awareness/mindfulness, as the increase in mindfulness is associated with decreased distress and other psychological symptoms. We will use a 17-item Five-Facet Mindfulness Questionnaire that measures five aspects: non-reactivity to inner experience, observing, acting with awareness, describing with words, and non-judging of experience. The original English version of the scale
^
34
^ is translated into Marathi and is included in the supplementary file (
*Extended Data*
^
17
^).

**
*Pregnancy outcomes*
**

We will gather information about the outcome of pregnancy (normal birth/stillbirth), whether the delivery took place at-term, and the birthweight of newborn based on the hospital records.

**
*Self-report log*
**

Participants in both arms will document any injuries or non-serious adverse events during the trial in the yoga journal (and a similar journal will be given to the participants in the EUC arm). IC and
*Sahayoginis* will keep track of this and report to the CRC in case of adverse events.

**
*Economic evaluation*
**

In the future explanatory trial, we plan to assess the cost-effectiveness of the YS intervention relative to the EUC. Effectiveness/health outcomes will be estimated using the Quality Adjusted Life Years based on the EQ-5D-5L data collected at the baseline and three months post-randomization. Costs will comprise intervention costs, healthcare resource costs, and wage loss costs. In this pilot trial, we will explore the feasibility of using the Client Service Receipt Inventory to estimate healthcare resource costs and wage loss costs. Intervention costs will be estimated using the trial records.

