**Methods:**

We will undertake a single-blind individual randomized parallel group-controlled pilot trial with 1:1 allocation ratio. Adult women with 12–26 weeks of pregnancy, without any obstetric or medical complications will be randomly allocated to either the active intervention group (Yoga-Sanskar (YS)) or the Enhanced Usual Care (EUC) group. Trained yoga instructors will teach a pre-defined yoga sequence to the participants in the YS arm. In the EUC arm, participants will receive a single session of health education. We will assess trial feasibility using the recruitment, retention, and study completion rates. The primary outcome of depression will be measured using the translated Marathi version of the Patient Health Questionnaire-9. Assessments will be at the baseline, three-months post-randomization, and post-delivery.

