*Sahayoginis* will maintain the intervention delivery log. The logs will be in paper format, and at the end of every week, RAs and IC will enter all the data on an access-restricted computer. We will save the data in password-protected CSV files. Process data for feasibility assessment will be obtained from the above logs.

Trial participants will complete a structured satisfaction survey at the end of the training and the final assessment sessions. We will conduct In-Depth Interviews with trial participants and yoga instructors. These interviews will focus on the intervention’s delivery, content, comfort, and complexity. We plan to enroll around 20 participants (12-13 from the YS arm and 7-8 from the EUC arm). However, data saturation will determine the final sample size for the qualitative study. Quantitative data obtained from the satisfaction survey (details below) and qualitative data from the IDIs will inform the acceptability of the intervention.

The description of measures that will be used to assess the preliminary efficacy of the intervention is given in
Table 2.

**Table 2. T2:** Measures to assess the preliminary efficacy.

Outcome	Measure	Time-point
Depression	Patient Health Questionnaire-9	Baseline, One, two, and three-months post-randomization, and post-delivery
Anxiety	Generalized Anxiety Disorder-7	Baseline, three-months post-randomization, and post-delivery
Stress	Perceived Stress Scale (PSS)	Baseline, three-months post-randomization, and post-delivery
Quality of Life	EuroQoL 5 Dimensions Score (EQ-5D-5L)	Baseline, three-months post-randomization, and post-delivery
Minor ailments in pregnancy	Common Symptoms in Pregnancy (CSIP)	Baseline, three-months post-randomization, and post-delivery
Experience of pregnancy	Pregnancy Experience Scale	Baseline, three-months post-randomization, and post-delivery
Attitude	Attitude towards Yoga practice during pregnancy scale	Baseline, three-months post-randomization, and post-delivery
Treatment Expectation	Credibility Expectancy Questionnaire	Three to four weeks post-randomization
Self-Efficacy	Yoga Sequence Self-Efficacy Assessment Yoga Practice Self-Efficacy Assessment	Three to four weeks post-randomization
Competence	Yoga Performance Assessment Scale Online Structured Competency Assessment	Three to four weeks post-randomization
Awareness	Five Facet Mindfulness Questionnaire	Baseline, three-months post-randomization, and post-delivery

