Satisfaction	Structured Questionnaire	Three to four weeks post-randomization and 3-months post- randomization
Home Practice	Self-report log	Every day
Injuries due to yoga	Self-report log	Every week for Three-months post-randomization
Serious Adverse Events (SAE)	SAE report form	Baseline, three-months post-randomization, and post-delivery

**
*Depression*
**

Depression during pregnancy is the primary outcome to assess the efficacy of the intervention. We will assess depression using a culturally adapted and validated Marathi version of PHQ-9. PHQ-9 is a nine-item tool to screen depression based on the Diagnostic and Statistical Manual-IV criteria (DSM-IV)
^
16
^. The Marathi version of the tool is in the supplementary file (
*Extended Data*
^
17
^).

**
*Anxiety*
**

GAD-7 is a seven-item tool to screen anxiety, also based on the Diagnostic and Statistical Manual-IV criteria (DSM-IV)
^
18
^. The Marathi version of the tool is in the supplementary file (
*Extended Data*
^
17
^).

**
*Stress and Social Support*
**

We will use a shorter (10-item) version of the original Perceived Stress Scale with 14 items
^
15
^ to assess perceived stress and the Multidimensional Scale of Perceived Social Support to assess perceived social support
^
19
^. PSS-10 measures participants' appraisal of various life situations in the last month and how unpredictable, uncontrollable, and overloaded they felt due to these situations. PSS and MSPSS are widely used in research studies across the globe, and they have acceptable psychometric properties
^
20,
21
^. In this study, we will use the Marathi version of the PSS and the MSPSS that were translated from the English versions using the World Health Organization (WHO) guidelines to translate and adapt instruments
^
22
^. The Marathi versions of the tools are uploaded in the supplementary file (
*Extended Data*
^
17
^).

**
*Quality of Life*
**

We will measure Health-Related Quality of Life (HRQoL) using the European Quality of Life Five Dimension (EQ-5D-5L) (
https://euroqol.org/eq-5d-instruments/all-eq-5d-versions/) descriptive system. We will generate a single utility score using the value set/preference weights for the Indian population
^
23
^. Participants will also rate their overall health using a visual analog scale (VAS). We will use the Marathi version of EQ-5D-5L with permission from the EuroQoL Group
^
24
^. The EQ-5D has been validated in different parts of the world
^
25
^.

**
*Minor ailments during pregnancy*
**

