### Assignment of interventions: allocation

**
*Sequence generation*
**

Serially numbered, opaque, sealed envelopes (SNOSE) will be used for treatment allocation. Clinical Research Coordinator (CRC) based in the Directorate of Research, PIMS will prepare SNOSE using the randomization list created by the trial statistician who will independently generate the randomization list using the statistical program
R (version 3.6.1). First, a list of variable block sizes (randomly selected block sizes of 2/4/6/8) will be created, followed by a list of intervention allocation (YS or EUC) using a 1:1 allocation ratio. CRC and trial statistician will be independent of the study team and will not interact with the RAs or the IC.

**
*Allocation concealment mechanism*
**

The IC will randomly allocate participants to the intervention group using SNOSE after they complete their baseline assessment.

**
*Implementation*
**

The IC will collect a set of opaque sealed envelopes from CRC as per the serial numbers a few hours before the recruitment. The IC will open the opaque sealed envelopes (as per the serial numbers) in front of the participants and immediately inform them about the intervention group (i.e., YS or EUC) assigned to them. Participants will be asked to keep their group assignment private from the RAs at the three-month follow-up, and post-delivery assessments. To maintain allocation concealment, neither the RAs nor any staff working at the hospital will have access to the randomization lists. The IC will inform the CRC of the unique identification number of the participant (and no other details) and the intervention allocation group. The CRC will maintain the record of intervention allocation.

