### Assignment of interventions: blinding

**
*Who will be blinded?*
**

Participants, their family members, and study team members involved with intervention delivery (IC and yoga instructors) will be aware of participants’ assigned intervention during the trial. It is not possible to avoid bias arising due to this. RAs will complete baseline, three-month follow-up, and post-delivery assessments, and they will not interact in any way with the intervention team. RAs will not be aware of the intervention allocation status. Participants and family members will be instructed not to disclose whether they are receiving YS intervention or EUC to the RAs at the time of the follow-up assessments. Additionally, RAs will also remind participants not to reveal their group assignment to them so that they remain blind to the participant’s treatment allocation.

Obstetricians will not be aware of the intervention allocation status, minimizing the risk of any change in their behavior while dealing with the participants.

The intervention team led by the IC and the outcome assessment team comprising RAs will not have any interactions during the trial. They will work independently of each other in separate locations and will have no communication about trial participants and their intervention allocation status. During the training of RAs in the outcome assessment team, particular emphasis will be given to explaining the equipoise between the two interventions.

We will monitor the risk of contamination at the level of the yoga instructors, intervention coordinator, and participants. Yoga instructors and the intervention coordinator will be requested not to share the information about YS with pregnant women other than those enrolled in the intervention arm. They will also ensure that participants in both the arms adhere to the group randomly allocated to them.

**
*Procedure for unblinding if needed*
**

If there is any yoga-related adverse event, we will reveal the intervention group allocation to the obstetrician.

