### Data collection and management

**
*Plans for assessment and collection of outcomes*
**

Research Assistants (RAs) will utilize Case Record Forms (CRF) to gather information during the initial assessment and the three-month follow-up. Data collection will be conducted using pen and paper, with subsequent manual entry into Microsoft Excel for digital conversion. The data will be stored as a CSV file, with original timestamps for entries and a record of any subsequent modifications in an audit trail. Documentation concerning the fidelity and quality of yoga intervention delivery will follow a similar process, with data stored in CSV format. Qualitative data will be recorded using digital voice recorders, and accompanying memos and field notes will be transcribed from Marathi to English for analysis. Data will be anonymized but associated with the trial ID.

The Clinical Research Coordinator (CRC) will conduct weekly checks on each data source for accuracy, consistency, and completeness, promptly addressing any queries and updating the database while maintaining an audit trail. Initially, separate databases will house distinct data types, with consolidation into a master database upon completion of data collection. Password protection will safeguard the data, with exclusive access granted to the CRC and no other trial team members.

**
*Plans to promote participant retention and complete follow-up*
**

During the initial assessment, RAs will inform the participants about the date for the three-month follow-up evaluation. RAs will call the participants one week before the follow-up assessment to remind them about the assessment. If the participant is traveling or is unavailable for any reason, there will be a seven-day window following the due date to complete the assessment. The assessments will be conducted preferably at the health center or Anganwadi center. If the participant is unable to come there, then the RA will complete the assessment at participant’s home.

**
*Data management*
**

We will prepare a Trial Master File that will encompass all vital documents. Documentation pertinent to the trial will be preserved for seven years following its conclusion. After this period, paper-based data will be securely disposed of, while electronic data will be purged of identifiable information.

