### Statistical methods

We will first compute the descriptive statistics for demographic, socio-economic, pregnancy-related characteristics, and outcome measures for all the trial participants in both arms. Descriptive statistics will include means and standard deviations (for continuous variables) or proportions (for discrete variables). We will use a t-test and chi-square test to compare means and proportions, respectively, to estimate the difference in the baseline characteristics between the two arms. We will use the intention-to-treat analysis to assess preliminary efficacy, binomial regression models to estimate risk ratios and 95% confidence intervals for binary outcomes and linear regression models to estimate regression coefficients for continuous outcomes. Analyses of continuous outcomes will additionally adjust for the baseline value of that outcome and any imbalances of baseline values of key covariates. The trial statistician will conduct the statistical analyses in
Stata version 18.

**
*Methods for additional analyses (e.g., subgroup analyses)*
**

*Process evaluation analysis*

We will audio-record all the in-depth interviews (IDIs) and focus group discussions and maintain field notes. Interviews in English will be transcribed verbatim, while those conducted in Marathi will be transcribed and translated into English. Team members proficient in both English and Marathi will conduct back-translation checks. Qualitative data will undergo analysis using the content analysis method. An initial coding framework comprising overarching themes will be established a priori. Subsequent themes will emerge from the data through inductive reasoning. NVivo 9 software (QSR) will facilitate data coding. The Principal Investigator will primarily oversee data analysis and synthesis of findings.

**
*Methods in analysis to handle protocol non-adherence and any statistical methods to handle missing data*
**

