Complier Average Causal Effect (CACE) analysis will be carried out to assess the effect of receiving treatment as defined in the protocol. CACE will be done in two ways. Full compliance is defined as attendance at the first five sessions and completing all the competency assessments. The first type of analysis will involve fully compliant participants. In the second type of analysis, participants with any compliance (attendance at one yoga session or more) will be included. The extent and pattern of missing data for each outcome will be explored. Multiple imputation of missing values will be performed if there are more than 10% missing values at endpoint.

**
*Plans to give access to the full protocol, participant level data and statistical code*
**

The trial protocol will be submitted to an open access journal before the initiation of participant enrollment. Additionally, the trial protocol and the supplementary files will also be uploaded on a dedicated website:

https://rahulshidhayelab.in/YOGA_D/

Six months after the completion of the trial, data will be uploaded on an open access data repository (e.g., Figshare) along with the statistical code used for the analysis.

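### Months 1 and 2 of the PHQ-9 appear only in Table 2, with no blinded collector named and no role in the stated analysis, and imputation depends on a 10% cut-off

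*Protocol article*

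**What the plan says.** The protocol article states: "Depression during pregnancy is the primary outcome to assess the efficacy of the intervention". It measures depression with the PHQ-9 and attaches no time point to that sentence. Table 2, under Outcomes, gives the PHQ-9 schedule as "Baseline, One, two, and three-months post-randomization, and post-delivery". The anxiety, stress and quality-of-life rows of the same table have no month 1 or month 2.

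Other sections describe fewer visits:

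- Abstract, Methods: "Assessments will be at the baseline, three-months post-randomization, and post-delivery".
- Blinding: "RAs will complete baseline, three-month follow-up, and post-delivery assessments".
- Allocation, Implementation: "Participants will be asked to keep their group assignment private from the RAs at the three-month follow-up, and post-delivery assessments".
- Data collection: research assistants (RAs) use case record forms "to gather information during the initial assessment and the three-month follow-up".
- Informed consent asks for separate consent at three months and after delivery. The retention text gives a reminder call and a seven-day window for the three-month visit only.

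For analysis, the Statistical methods section plans "linear regression models to estimate regression coefficients for continuous outcomes", adjusted for the baseline value and for imbalanced key covariates. On missing data it says: "Multiple imputation of missing values will be performed if there are more than 10% missing values at endpoint". It does not define that endpoint.

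**The concern.** Two things are left open on the primary efficacy measure.

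**Who collects months 1 and 2, and are they blinded?** The trial relies on blinded RAs to limit assessment bias, yet the text assigns them only baseline, three months and post-delivery. Because the outcome is depression during pregnancy with no time point named, the month-1 and month-2 scores could count towards it.

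**How are missing scores handled?** Whether imputation is used depends on the observed share missing. At or below the cut-off none is planned, so a regression at a single time point uses only the women observed there. If women leave because of how they felt at an earlier assessment, and this differs by arm, that estimate is biased. Participants know their allocation, so such a difference is plausible. Scores that could reduce the bias are already in Table 2, but the stated analysis does not use them.

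**Working it through.** **1. The schedule, side by side**

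| Place in the protocol article | Follow-up named |
|---|---|
| Table 2, PHQ-9 row | months 1, 2, 3; post-delivery |
| Abstract, Methods | month 3; post-delivery |
| Informed consent | month 3; post-delivery |
| Allocation, Implementation (non-disclosure) | month 3; post-delivery |
| Blinding (RA assessments) | month 3; post-delivery |
| Data collection (case record forms) | month 3 |
| Retention (reminder and window) | month 3 |

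Only Table 2 has months 1 and 2. Of the three antenatal follow-up scores (months 1, 2, 3), one has a named blinded collector and two do not.

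**2. The imputation trigger**

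Inputs: 25 per arm, 50 in total (Sample size section); cut-off above 10% (Statistical methods). The planned 50 agrees with the screening figure: 600 × 0.10 × 0.85 = 51.

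10% of 50 is 5, so the trigger needs 6 or more missing. With true missingness p, the chance that it fires is 1 − Σ C(50,k) p^k (1−p)^(50−k), summed over k = 0 to 5. The protocol gives no expected missingness at follow-up, so p is a range:

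| Assumed p | Chance of 6 or more missing |
|---|---|
| 5% | 4% |
| 10% | 38% |
| 15% | 78% |
| 20% | 95% |
| 25% | 99% |

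**3. What months 1 and 2 could add**

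The protocol gives no correlations. Assume one correlation ρ among baseline and months 1 to 3. With k earlier scores, the share of month-3 variance predicted is kρ² / (1 + (k−1)ρ).

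| ρ | Baseline only (k = 1) | Baseline and months 1, 2 (k = 3) |
|---|---|---|
| 0.3 | 0.09 | 0.27/1.6 = 0.17 |
| 0.5 | 0.25 | 0.75/2.0 = 0.38 |
| 0.7 | 0.49 | 1.47/2.4 = 0.61 |

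**4. Size of the possible bias (illustrative simulation)**

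Assumptions: no true effect, 25 per arm, correlations 0.35 to 0.65, and dropout that depends on the month-2 score with a strength differing by arm.

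- Without imputation, about 8 to 10% missing: bias roughly 0.05 to 0.10 SD, depending on how far the arms differ.
- Same setting, using months 1 and 2: bias within about 0.012 SD of zero.
- Dropout depending on month 2 identically in both arms: bias about zero even without imputation.
- Dropout depending on the unseen month-3 score: using months 1 and 2 still leaves 0.05 to 0.10 SD at 9 to 10% missing and 0.10 to 0.22 SD at 19 to 21%.

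The spread of the estimate at about 10% missing was 0.286 SD. The bias is therefore 0.05/0.286 = 0.17 to 0.10/0.286 = 0.35 standard errors. A shift of 0.35 takes 95% interval coverage to Φ(1.61) − Φ(−2.31), about 93.6%.

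**The case against.** Several points on the other side stand.

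- **The schedule lists are loose.** The data-collection text omits even the post-delivery visit, so these lists are not exhaustive. Figure 1 is not available and may show the monthly PHQ-9. Neither removes the conflict with Table 2.
- **Unblinded collection is not stated.** A reader might infer it, because the intervention coordinator, yoga instructors and *Sahayoginis* are the staff in regular contact between visits. The protocol does not say that they administer the PHQ-9. It names nobody. In addition, the PHQ-9 answers come from women who know their allocation, a limit that the blinding section accepts.
- **The intermediate scores are not said to be discarded.** The regression sentence is generic to all continuous outcomes. A separate analysis plan could use a repeated-measures model or put months 1 and 2 in the imputation model. It would still have to override the published 10% rule, and it could not by itself settle who collects the data under what blinding.
- **The model does not change at the cut-off.** Baseline-adjusted regression applies on both sides; only the handling of missing values switches. If only the outcome is missing and the imputation model holds the same covariates as the analysis, the two estimates agree in expectation. The switch matters for bias only when the imputation model contains more, such as months 1 and 2.
- **Larger bias figures do not describe this plan.** A complete-case analysis at about 20% missing would be off by more (0.11 SD in one such simulation), but there the rule imputes 95% of the time. With months 1 and 2 in the imputation, a simulation of the stated rule gave 0.001 to 0.004 SD at 19 to 21% missing and 0.03 to 0.04 SD at 9 to 10%.

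**Conclusion.** The point holds in a limited form. The schedule of the primary measure contradicts itself, no blinded collector is named for two of three antenatal follow-up scores, and imputation depends on whether 5 or 6 of 50 women are missing at an undefined endpoint. These follow from the text, with 50 randomised.

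The bias of roughly 0.05 to 0.10 SD applies to analysis without imputation at about 10% missing. It rests on assumed correlations and on dropout that follows earlier scores differently by arm. At 0.17 to 0.35 standard errors it is small, and this is a pilot with preliminary efficacy aims. It would be too strong to say that months 1 and 2 remove dropout bias: they do so only when dropout is driven by scores that were observed.

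The change is still worth making. Preliminary efficacy is among the primary objectives, the procedures are meant to carry into the explanatory trial, and the correction is cheap.

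**What to change.** 1. **Reconcile the schedule.** Make Table 2 agree with the abstract, consent, allocation, blinding and data-collection sections. If months 1 and 2 are kept, state that blinded RAs collect them, extend the non-disclosure request to those contacts, and state the mode of collection, since the three-month visit is planned in person. If they are not kept, remove them from Table 2.
2. **Name one efficacy time point: three months post-randomization.** The last antenatal score is a different target and should not be used interchangeably. A woman enrolled at 26 weeks and randomised about a week later reaches three months at about 26 + 1 + 13 = 40 weeks and may have delivered, so say how such scores are treated.
3. **Delete the 10% trigger and pre-specify one analysis whatever the share missing.** Either of these would do:
   - a mixed model for repeated measures with months 1, 2 and 3, arm by month, baseline PHQ-9 and all randomised women, reporting the month-3 contrast; or
   - multiple imputation with months 1 and 2 in the imputation model.

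   If months 1 and 2 are dropped, one fixed method for the month-3 score is still needed.

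Cost: revised wording, a little more analysis work, and RA time for two short assessments per woman that Table 2 already schedules. The extra RA contacts during the intervention also add occasions on which allocation could be disclosed, which is why the non-disclosure request must cover them.
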